**Figure 4 Fig4:**
[figure not shown]
**Patient follow-up visit schedule.** *The HRCT scanned for the screening process can be acquired up to 90 days before randomization. FU = follow-up.

### Analysis

A two-sample t test was used to determine the sample size for the study based on the two primary endpoints. An assumption of a 12% predicted difference in FEV_1_ between the treatment arm and the control arm at 12 months with an assumed standard deviation of 15 leads to an intended sample size of 59 patients. An assumption of an 11 point difference in SGRQ between the treatment arm and the control arm at 12 months with a standard deviation of 14 leads to an intended sample size of 60 patients. However, to account for an estimated 15% loss during patient follow-up, the sample size was increased by 15% resulting in an intended sample size of 69 patients. The sample size was calculated using an 80% power, a Type I error rate of 0.05 and a 2:1 randomization allocation. The calculation was computed using Power Analysis and Sample Size 11 software.

The Hochberg method will be utilized to compensate for the multiple comparisons resulting from two endpoints and evaluate if the primary endpoint has been reached. The Hochberg method allows for two different scenarios to determine achievement of the primary endpoint for a positive trial:If both primary endpoints (FEV_1_ %predicted and SGRQ) reach clinical significance at the 0.05 level.

OR2.If either one of the two endpoints (FEV_1_ %predicted or SGRQ) reach clinical significance at the 0.025 level.

Additionally, a binary responder rate analysis will be performed, where a responder is identified for the following secondary endpoints as:

%predicted FEV_1_ ≥ 12% difference from baselineSGRQ ≥ 8 points difference from baseline6MWT ≥ 30 meters from baseline

Primary endpoint analysis will be based on the 12 month visit. If data is not available due to a serious adverse event, including death, then the worst prior follow-up value will be used. If data is missing in other cases, the last available value from prior visits will be used. If no follow-up data is available, an intent-to-treat analysis will use the baseline values. A sensitivity analysis will be presented excluding such patients.

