### Primary and secondary endpoints

The STEP-UP primary endpoints are the change in FEV_1_ (% predicted) and SGRQ score between the treatment and control arm at 12 months. Adverse events will be monitored over the course of the study and be considered as secondary endpoints along with other efficacy outcomes at 6 and 12 months such as lung volumes, mMRC, SGRQ, DLCO, 6MWT. LVR from a 6 month follow-up HRCT will also be a secondary efficacy endpoint for the treatment group.

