[24]. This indicates that LVR is most beneficial when reducing the most diseased portions of the lung. Because LVR has traditionally been induced at the lobar level, heterogeneity has also traditionally been defined as the difference in disease state between ipsilateral lobes. However, because the STEP-UP trial targets individual segments for treatment, it is important to apply the idea of heterogeneity at the segmental level. Segments within a lobe are not necessarily equivalently diseased and applying heterogeneity at the segmental level determines a segment’s disease state in comparison to the remaining lobe as well as disease state in comparison to the ipsilateral lower lobe. This helps in identifying the segment that is least contributing to healthy pulmonary function or conversely most contributing to poor pulmonary function. The segments that are relatively less diseased in comparison to the remaining emphysematous upper lobe and lung positively contribute to pulmonary function and should therefore be conserved.

If we look to the future potential of bronchoscopic LVR in general and vapour therapy in particular we note that 1) due to the progressive nature of emphysema, the segments are expected to worsen overtime causing pulmonary function to decline, 2) because not all segments are treated during the STEP-UP trial, the segmental approach may potentially also be utilized in the future as a follow-up treatment for patients who have previously been treated for emphysema and 3) a focused segmental approach across all affected lobes might elucidate therapeutic targets in whole patient populations previously generalized as having a diffuse disease.

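### The imputation rules for both primary endpoints cannot score a death or a loss to a serious adverse event below earlier measurements, so treatment harm can enter the 12-month comparison as no change or as gain

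*Protocol article*

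**What the plan says.** The section on primary and secondary endpoints defines the target: "The STEP-UP primary endpoints are the change in FEV_1_ (% predicted) and SGRQ score between the treatment and control arm at 12 months". The Analysis section fixes the time point ("Primary endpoint analysis will be based on the 12 month visit") and then gives three rules for missing values:

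- Death or SAE: "If data is not available due to a serious adverse event, including death, then the worst prior follow-up value will be used".
- Other reasons: "If data is missing in other cases, the last available value from prior visits will be used".
- No follow-up at all: "If no follow-up data is available, an intent-to-treat analysis will use the baseline values".

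One check on these rules follows: "A sensitivity analysis will be presented excluding such patients". Harm is otherwise assigned to the secondary endpoints: "Adverse events will be monitored over the course of the study and be considered as secondary endpoints".

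**The concern.** Every imputed value is one the patient already had. A treated patient who dies before any follow-up measurement receives a change of zero. A patient whose follow-up values were all above baseline before a fatal event receives a gain, because the worst of several gains is still a gain. No rule lets the event itself lower the score.

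The rules are the same in both arms, but the exposure is not. Treated patients have two ablation sessions and controls have no sham procedure, so procedure-related events can fall only in the treatment arm. If they do, the primary comparison credits that arm with results those patients did not have at 12 months. The trial can be declared positive on one endpoint alone at the 0.025 level, so a modest shift in either mean could affect the conclusion.

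**Working it through.** **Planned figures.** The Analysis section assumes an FEV1 difference of 12 (SD 15) and an SGRQ difference of 11 (SD 14), with 80% power, type I error 0.05 and 2:1 allocation. A two-sided two-sample t calculation reproduces the sample size to within rounding. For FEV1, 39:20 (59 patients) gives 81.6% power. For SGRQ, 40:20 (60 patients) gives 80.5%. Then 60 × 1.15 = 69, which splits 46:23. The sample size is not in question; 46 and 12 are carried forward as the yardsticks.

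**Inputs that are assumptions.** The article does not say how many patients will lack 12-month data because of death or an SAE, or what their true change would be. Take k = 3 to 7 of 46 treated patients. The upper end equals the plan's overall loss allowance (15% of 46 = 6.9), and not all of that loss would come from SAEs. Take a true change of -10 on a scale where positive is better, and no control events.

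**Formula.** Excess in the treated mean = (k/46) × (imputed change - true change).

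| Case (FEV1) | Gap | k = 3 | k = 5 | k = 7 |
|---|---|---|---|---|
| Baseline carried: 0 - (-10) | 10 | 0.65 | 1.09 | 1.52 |
| Planned gain carried: 12 - (-10) | 22 | 1.43 | 2.39 | 3.35 |

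Against the planned 12, the first row is 5% to 13% (0.65/12, 1.52/12) and the second is 12% to 28% (1.43/12, 3.35/12).

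**SGRQ on the same assumptions.** Carrying baseline gives 0.65 to 1.52 points. Carrying a gain of 11 has a gap of 21 and gives 1.37 to 3.20 points, against a planned 11.

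**Control events.** If controls are affected with the same gap, the bias in the difference is gap × (k_T/46 - k_C/23). It vanishes when the two proportions are equal. With 7 treated and 1 control affected and a gap of 10, it is 10 × (7/46 - 2/46) = 1.09. Only the imbalance matters.

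**The opposite direction.** If affected patients would truly have shared the planned benefit and controls do not change, carrying baseline lowers the expected FEV1 difference to 12 × (46 - k)/46, which is 11.2 at k = 3 and 10.2 at k = 7.

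**The stated sensitivity analysis.** With a mean gain of 12 in the remaining treated patients, excluding the affected ones leaves the difference at 12 whatever happened to them. The words that identify the excluded patients could mean everyone with an imputed value or only those with no follow-up. On the first reading the harmed patients are dropped. On the second, the worst-value and last-value rules are never examined. Neither reading tests the assumption.

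**The case against.** The strongest defence is that the worst-value rule already penalises. It is harsher than the last-value rule used elsewhere, it records harm whenever a measured value fell below baseline, and it would usually make the carried-gain figures smaller than shown. Baseline imputation can dilute a true benefit, so the direction is not uniform. The rule applies to both arms, and only when an SAE has made the 12-month data unavailable; many patients with an SAE may still attend. Safety is also reported as a secondary endpoint and overseen by an independent DSMB and CEC, so the harm is not hidden from the trial. Further sensitivity analyses may stand in an SAP that is not shown. All of this limits the size of the problem. It does not remove it, because the article itself fixes the primary rule, and that rule has no score worse than the measurements before the event.

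Several stronger readings are tempting but not supported:

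- A reader might infer that the worst prior value will usually be a single 6-month value. The article names 6 and 12 months for secondary outcomes, lists eight clinic visits, and puts the schedule in a figure that is not available. The measurement visits for the primary endpoints are therefore unknown.
- A reader might infer that responder rates are biased as written. The imputation rules follow the sentence on the primary analysis; nothing says that imputed values feed the responder analysis.
- A reader might score death as a loss of 30 FEV1 points and obtain larger shifts. Entry FEV1 is 20% to 45% predicted, so anyone entering below 30 would go negative.
- A reader might take surviving controls to decline measurably by 12 months. The Discussion says "due to the progressive nature of emphysema, the segments are expected to worsen overtime causing pulmonary function to decline", but as a remark on future potential and without a 12-month rate.
- A reader might want a site-stratified worst-rank test as the primary analysis. With 69 patients at up to 17 sites (69/17 is about 4 per site), and a target no longer the mean difference used for the sample size, that is debatable.

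**Conclusion.** The concern holds in limited form. As written, the rules can enter a death or SAE loss as no change or as improvement in both primary endpoints, and the one stated sensitivity analysis does not test this. An excess of such events in the treatment arm would bias the comparison toward treatment.

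With 3 to 7 of 46 treated patients affected, no control events and a true FEV1 change of -10, the treated mean is too high by about 0.7 to 1.5 units (baseline carried) or 1.4 to 3.3 units (a gain of 12 carried), against a planned difference of 12. The count, the true change and the absence of control events are assumptions. The worst-value rule may reduce the second range, and where affected patients would truly have benefited, baseline imputation works against treatment.

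**What to change.** 1. For data missing for reasons other than death or an SAE, replace last-value and baseline carry-forward with a mixed model for repeated measures, or multiple imputation, using arm, baseline and the visits at which the endpoints are measured.
2. For death and SAE-precluded data, cap the imputed value so that it is never better than baseline. The cap removes gains but still permits a score of no change, so pre-specify alongside it a sensitivity analysis that scores these patients at the worst change observed in either arm, or by worst rank.
3. Keep the exclusion analysis, state which patients it leaves out, and add control-based imputation and a tipping-point analysis.
4. State that patients who die or lack 12-month data because of an SAE count as non-responders.

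The cost is analysis-plan wording and some programming, with no new patients or measurements. The estimate may become less favourable to treatment.

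### The one sensitivity analysis the article states removes patients because of events after randomisation, so it does not test less favourable values for lost patients and may lean towards treatment

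*Protocol article*

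**What the plan says.** The Analysis section of the protocol article bases the primary analysis on month 12 and gives three single-value rules for missing data.

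- **SAE or death:** "If data is not available due to a serious adverse event, including death, then the worst prior follow-up value will be used".
- **Other missing data:** the most recent earlier value is carried forward.
- **No follow-up data at all:** the baseline value is used, which means a change of zero.

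The section then closes with "A sensitivity analysis will be presented excluding such patients". No other sensitivity analysis appears in the article, and the group to be excluded is not defined further.

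**The concern.** A sensitivity analysis of missing data should show whether the result survives assumptions about lost patients that are less kind to the treatment. This one takes those patients out.

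The reason for removal arises after randomisation and may be caused by treatment. The Background and Table 1 link SAEs to the volume of lung ablated: in the earlier vapour ablation trial the rate was 54% above 1700 ml and 10% below. Control patients have no study bronchoscopy, so losses caused by the procedure can occur only in the treated arm. On the broad reading, the check also replaces a rule that scores SAE and death losses at their worst earlier value with one that does not score them at all.

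At stake is what agreement between the two analyses would mean. It could be taken as robustness although no worse value for a lost patient had been tried. The undefined group is a second weakness: in an open-label trial, the analysed set should be fixed before the data are seen.

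**Working it through.** **Inputs from the Analysis section.** "The sample size was calculated using an 80% power, a Type I error rate of 0.05 and a 2:1 randomization allocation"; for FEV1, a 12-point difference and "an assumed standard deviation of 15 leads to an intended sample size of 59 patients"; for SGRQ, an 11-point difference "with a standard deviation of 14 leads to an intended sample size of 60 patients"; and finally "the sample size was increased by 15% resulting in an intended sample size of 69 patients".

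**Reproducing the plan's own figures.** A two-sided two-sample t test at 2:1 needs 19.06 controls for FEV1 (20 + 39 = 59) and 19.73 for SGRQ (20 + 40 = 60). Then 60 × 1.15 = 69, which is 46 treated and 23 control. The stated sizes reproduce. They supply the arm sizes and SDs used below.

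**Assumptions not in the documents.** The article gives only 15% loss overall. Loss by arm, and the correlation ρ between being lost and the month-12 outcome, are assumed and varied.

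**Closed form.** If a fraction f of one arm is removed from the unfavourable end, the mean of the rest shifts by ρ × SD × φ(z_f)/(1 − f). For f = 0.15, z = −1.036 and φ = 0.2332, so φ/(1 − f) = 0.2332/0.85 = 0.274.

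- FEV1: 0.274 × 15 = 4.1 points at ρ = 1, and 2.1 at ρ = 0.5.
- SGRQ: 0.274 × 14 = 3.8 points at ρ = 1, and 1.9 at ρ = 0.5.

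**Simulation of the exclusion analysis.** 46 v 23, SD 15, no true effect, a fixed number dropped, t test on the rest. Each cell gives the spurious FEV1 benefit and the share of trials with p<0.05 favouring treatment (nominal 2.5%).

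| Treated dropped | Controls dropped | ρ = 0.5 | ρ = 1 |
|---|---|---|---|
| 1 | none | +0.35, 3.2% | +0.7, 4.3% |
| 2 | none | +0.7, 4.1% | +1.4, 6.4% |
| 5 (about 10%) | 3, at random | +1.5, 6.1% | +3.0, 14.4% |
| 7 (about 15%) | 3, at random | +2.0, 7.9% | +4.1, 22.4% |
| 7 | 3, same mechanism | +0.3, 3.2% | +0.6, 6.2% |

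At ρ = 0 there is no bias and the rate is about 2.5%. In the last row the loss is not quite equal, because rounding gives 7/46 = 15.2% against 3/23 = 13.0%. Trimming a fixed number of extreme values also makes the t test understate its variance, which raises the rate at ρ = 1.

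**Second simulation, with the number lost free to vary.** The primary rule for SAE and death was run alongside, assuming a correlation of 0.7 between visits.

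- Loss 15% treated, 5% control: exclusion gives +1.2 points (5.1%) at ρ = 0.5 and +2.5 (11.6%) at ρ = 1.
- Loss 22.5% treated, 0% control (10.35 of 69, or 15% overall): +2.9 (11.3%) and +5.8 (38.4%).
- Loss 15% in both arms by the same mechanism: no bias, 2.3% to 2.5%.
- Scoring at the worst earlier value: at or below about 2.6% in every scenario.

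Where loss is unequal and outcome-related, the check is therefore more biased towards treatment than the rule it is meant to support.

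**The case against.** **The narrow reading is natural.** The sentence follows directly on the rule for patients with no follow-up data. A reader might infer that all deaths and SAE losses are deleted, but the text does not establish this. On the narrow reading, a patient lost through an SAE who has an earlier value stays in at the worst of those values. With clinic visits from the first weeks onward, few patients should have no follow-up, although the article does not say which visits measure FEV1 or SGRQ. The first two rows of the table are then the relevant ones, against a planned difference of 12 points. This stands.

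**The bias is conditional.** Controls with severe emphysema may also die or be lost because of poor lung function. The larger figures need loss that is both unequal between arms and related to outcome, and the documents give neither quantity. This stands.

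**The check decides nothing.** Success rests on the primary analysis under the Hochberg rule, and that analysis keeps these patients. A reader might take 22% or 38% as the trial's false-positive rate. It is not.

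**A fuller plan may say more.** The article condenses a longer protocol, and the statistical analysis plan is not shown. One can say only that no other sensitivity analysis is stated here. The point still does not rest on an omission: the article names a method, and the method is a weak one.

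**The exclusion analysis has some use.** It shows how far the result depends on imputed values. It does not show what happens if those values were too favourable.

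**Conclusion.** The point holds in a limited form. The one sensitivity analysis stated here selects on an event after randomisation, leaves its excluded group undefined, and tests no less favourable value for lost patients on either reading.

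How far it leans depends on the reading and on the assumed loss. It is about 0.35 to 1.4 FEV1 units (3% to 6% favourable results) if one or two treated patients are dropped. It is about 2 to 4 units (8% to 22%) if 15% of the treated arm is dropped through outcome-related loss while control loss is random. It is close to nil if loss is equal and arises the same way in both arms. The number dropped, the split by arm and the correlation with outcome are all assumptions.

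The documents do not support saying that the primary test is compromised by this sentence, that every death and SAE loss is deleted, or that no other check is planned anywhere. The sentence should be revised, because agreement with this check would be weak evidence of robustness.

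**What to change.** 1. State which patients are excluded: everyone with an imputed month-12 value, or only those with no follow-up data.
2. Label the exclusion analysis as descriptive and do not cite it in support of the primary result.
3. Make the supporting sensitivity analysis one that keeps all randomised patients. One option is multiple imputation in which treated patients lost through SAE or death are drawn from the control-arm distribution. Add a tipping-point analysis that worsens those values by an increasing delta and reports, for each primary endpoint, the delta at which significance is lost.

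The cost is a short change to the text and modest programming, with no change to patients, visits or sample size. The downside is that the reported robustness may look less favourable.

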### Safety

A Data Safety Monitoring Board (DSMB) and Clinical Events Committee (CEC) are in place to closely and independently monitor the safety of the STEP-UP trial. Reports outlining these occurrences will be generated on a frequent periodic basis unless the DSMB/CEC requests the reports more often. DSMB/CEC will conduct a review at a minimum for the first and second treatment of the first 15, 30 and 46 patients.

## Discussion

The NETT established that although LVRS may lead to clinically relevant improvement for patients with ULPE, the treatment is also associated with a high risk profile. To minimize these risks, LVR can be induced bronchoscopically via vapour ablation. Pilot studies for vapour ablation, including the VAPOR trial, have demonstrated successful LVR and clinically significant improvement for patients treated unilaterally with vapour ablation
[5, 10]. The STEP-UP trial has been established to investigate a bilateral sequential segmental approach for vapour ablation and has been designed to conserve a balance between the treatment’s safety and efficacy profiles.

Vapour ablation treatment ablates emphysematous tissue resulting in a reduction of lung volume and hyperinflation. Each STEP-UP procedure will consist of two treatment sessions and each session will treat smaller volumes of lung in comparison to VAPOR. This is expected to reduce the occurrence of SAEs during the STEP-UP trial due to correlation defined previously between amount of lung treated per session and rate of SAEs. In addition to reducing the amount of energy delivered per session, treating over the course of two sessions typically allows a larger volume of lung to be treated during the entire procedure in comparison to the VAPOR trial. The increase in total volume treated per procedure is anticipated to improve efficacy while lessening the amount of energy delivered in one session is anticipated to improve safety.

The severity of disease of each segment targeted for treatment is also anticipated to affect the improvement in efficacy. Due to vapour ablation’s ability to treat in the presence of CV, the treatment can specify and target individual segments. The STEP-UP trial explores the approach of targeting only the most diseased segments for treatment of both upper lobes to allow the less diseased segments to continue lung functionality.

Furthermore, studies have demonstrated that the larger the heterogeneity, the more efficacious the outcomes are post-LVRS
[22, 23]. This has also held true for LVR induced via treatment using an alternate bronchoscopic method (endobronchial valves), where larger heterogeneity showed correlation with improvements in FEV_1_ and 6MWT
[24]. This indicates that LVR is most beneficial when reducing the most diseased portions of the lung. Because LVR has traditionally been induced at the lobar level, heterogeneity has also traditionally been defined as the difference in disease state between ipsilateral lobes. However, because the STEP-UP trial targets individual segments for treatment, it is important to apply the idea of heterogeneity at the segmental level. Segments within a lobe are not necessarily equivalently diseased and applying heterogeneity at the segmental level determines a segment’s disease state in comparison to the remaining lobe as well as disease state in comparison to the ipsilateral lower lobe. This helps in identifying the segment that is least contributing to healthy pulmonary function or conversely most contributing to poor pulmonary function. The segments that are relatively less diseased in comparison to the remaining emphysematous upper lobe and lung positively contribute to pulmonary function and should therefore be conserved.

If we look to the future potential of bronchoscopic LVR in general and vapour therapy in particular we note that 1) due to the progressive nature of emphysema, the segments are expected to worsen overtime causing pulmonary function to decline, 2) because not all segments are treated during the STEP-UP trial, the segmental approach may potentially also be utilized in the future as a follow-up treatment for patients who have previously been treated for emphysema and 3) a focused segmental approach across all affected lobes might elucidate therapeutic targets in whole patient populations previously generalized as having a diffuse disease.

